### Secondary outcomes

The secondary outcomes correspond to the maximum isometric muscle force measured by the manual dynamometer (Lafayette Instrument Company, Lafayette, IN, USA) and the level of satisfaction of the patient in relation to the treatment received, through two multiple choice questions.

Each outcome measure is described below:
Pain assessment

Pain will be assessed through the VAS [41, 42], with a scale of 0 (without pain) to 10 (extreme pain). The VAS will be applied considering two moments: (1) pain in the last month (current moment); and (2) before and after performing two functional activities: bilateral squatting at 90° (for 1 min) and step-up/down 26 cm (for 1 min).

The VAS is responsive, sensitive and valid to evaluate the PFP population [41, 42].
Functional assessment

To evaluate function, we will use the ADLS [43–45] and the AKPS [44, 46, 47] questionnaires. These instruments are considered reliable, responsive and valid for the population with PFP [44, 47]. The ADLS consists of three questions that measure the individual’s overall function level on a scale of 0–100. In addition, it has 14 items, which generally measure the symptoms and functional limitations caused by PFP in daily life activities. Moreover, AKPS has 13 items, which also evaluate the symptoms and functional limitations that are often present in individuals with PFP. In both questionnaires, the score ranges from 0 to 100, where 0 corresponds to the greatest functional impairment in relation to pain and 100 indicates no functional impairment.
Kinematic assessment

In the frontal and sagittal planes, the lower-limb kinematics will be evaluated during squatting [14, 22, 24, 33] through 2D shooting with two full HD camcorders (JVC GZ-E10, JVC, Wayne, NJ, USA). The cameras will be positioned frontal and lateral to the participant, at a distance of 2.5 m [48]. Evaluation of both lower limbs will be performed.

The static calibration of the system will be performed using a 160-cm-long stick. Subsequently, the patient’s bipodal static position will be recorded.

Self-adhesive labels will be positioned bilaterally in the following points: lateral malleolus and medial and anterior tibial tuberosities, lateral and medial epicondyles of the femur and anterior superior iliac spine, upper region of the iliac crest, and spinous process of the vertebra (chest T7, cervical vertebra C7, and the centre of the sternum).

To perform the single-leg squat test, the participants will remain in unipodal support with the contralateral limb to the side with the knee flexed at 90° and arms positioned at the waist. Deep squats will be performed without the contralateral foot touching the ground. The minimum squat angulation is 60°. If, during the test, some of the requirements are not fulfilled, the test will be invalidated and repeated.

For familiarization, the participant will be asked to squat twice with each leg, with a rest interval of 2 min between each movement. After familiarization, the participants will perform the single-leg squat three times consecutively, in which the average of the measured angles is considered for analysis. In the frontal plane, the following angles will be measured: dynamic valgus of the knee, pelvic tilt, and lateral flexion of the trunk. In the axial planes, the angles of anterior trunk flexion and knee flexion will be measured. The analysis of these angles will be performed by the Kinovea® program.
Strength evaluation

The measurement of the strength of knee extensors [49], abductors [15], lateral rotators [15], and hip extensors [15] will be obtained by means of an evaluation using the manual dynamometer (Lafayette Instrument Company, Lafayette, IN, USA) [50, 51]. An instrument that is valid and reliable [50].

To measure the strength of the knee extensors, the individual will be seated at the edge of the stretcher with the hips flexed at 90° and the knee to be tested at 60°. For the abductors, the individual will be positioned lying on their side, and the limb to be tested will be facing upwards, with neutral rotation of the hip, 10° of extension, and 20° of abduction [15]. For the lateral rotators, the individual will be seated at the edge of the stretcher with hips and knees flexed at 90° and will be oriented to perform slight lateral rotation so that the lateral malleolus is aligned with the midline of the body [15]. For the hip extensors, the individual will be in the prone position with the knee to be tested having 90° of flexion and 10° of extension [15].

The use of a stabilizing strap will be adopted during the tests to avoid the need to compensate, and to stabilize the dynamometer. Before performing the tests, the patient will be asked to perform two submaximal isometric contractions of each muscle group, for familiarization, with a 1-min rest to start the test. The patient will be asked to perform three maximum voluntary isometric contractions of each muscle group for 5 s. A 1-min rest period will be allowed between each measurement. During the conduct of all tests, the patient will be verbally encouraged using the words “Force, force, force!” For the analysis, we will consider the average strength of the test of each muscle group.
Level of satisfaction

This parameter will be measured during the reassessment of the patient, using a qualitative questionnaire composed of two multiple choice questions, elaborated exclusively by the principal investigator of the study. The purpose of this questionnaire was to measure the patient’s satisfaction with the treatment and their current clinical condition [6].

### Data analysis

The Kolmogorov-Smirnov normality test will be performed. If the null hypothesis is confirmed, parametric data for the comparisons will be used. However, if the null hypothesis is not confirmed, nonparametric tests will be conducted.

For parametric data, comparison between the groups will be carried out using linear mixed models, considering *P* values ≤ 0.05 as significant difference. For intragroup comparison (pre and post intervention), the analysis of variance (ANOVA) test will be used for repeated measurements, considering *P* values ≤ 0.05 as significant difference.

The clinical relevance of the results will be confirmed by calculating the effect size (Cohen’s d) of the significant differences. The following effects will be considered: 0.00–0.49, small; 0.50–0.79, medium; and above 0.80, large (Cohen, 1988). An intention-to-treat analysis will be performed [52].

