Conservative treatment for PFP has been focused on trunk- and hip-muscle-strengthening protocols associated with strengthening of the knee musculature [28–33], as pain reduction and motor function improvement were observed in these patients [28, 29, 34].

In view of the kinematic characteristics of this population, the integration of neuromuscular training to the strengthening protocol may be important. However, the evidence-base is poor and unclear [32, 33, 35–37]. We found only five studies that evaluated these phases of physical therapy in patients with PFP. One was a case report [32]; two studies observed the effect of motor control under dynamic alignment during gait [35, 36]; one study evaluated trunk and lower-limb kinematics following an isolated knee-strengthening and stretching program versus a hip-strengthening program associated with neuromuscular training [33]. Moreover, only one study evaluated the additional effect of neuromuscular training, concluding that the addition of neuromuscular training does not promote significant improvement in the kinematics of the trunk and lower limb [37]. However, the small sample size, relatively unchallenging motor-control protocol, and short, 4-week, intervention period could have influenced the results [37]. Therefore, ,studies that address neuromuscular training in the treatment of individuals with PFP are necessary.

Taking into account these aspects, the objective of this study was to evaluate the addition of neuromuscular training to the strengthening of the trunk, hip, and knee muscles on pain, functional capacity, and kinematics of the trunk, pelvis, and lower limb in patients with PFP. Our hypothesis is that, compared to the group that received only strength training, the group submitted to the protocol that combined neuromuscular strengthening and training would show greater improvement in pain, function, lower-limb and trunk kinematics, and strength of the hip and knee.

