### Participants and therapists

The sample size calculation was performed using the mean difference and standard deviation error (based on outcomes of pain; function; kinematics of the trunk, hip, and lower limb during the single-leg squat; and strength of the hip and knee) of similar studies in the literature. The power of the test considered was 80% and the alpha was 0.05, with a sample size of 45 per group. In this analysis, the program BioEstat version 5.3 (Manaus, Brazil) was used.

A total of 90 active female individuals aged 18–30 years who have anterior or retropatellar pain in the knee (with a Visual Analog Scale (VAS) score ≥ 3) [2, 33] for at least the last 3 months (in two or more of the following activities: running, walking, jumping, climbing up and/or down stairs, remaining seated or kneeling for a long period of time, squatting, during isometric extension of the knee with 60° of flexion, and during palpation of the medial or lateral facet of the patella) [33], and who perform any type of physical activity up to twice a week and/or are irregularly active A and B individuals according to the International Physical Activity Questionnaire (IPAQ), will be recruited [38]. The exclusion criteria are as follows: previous physical therapy treatment; history of knee surgery; patellar dislocation; ankle or hip injuries; meniscal or ligament injury; any other specific knee changes; tendinitis in the lower extremity; low back pain; sacroiliac joint pain; pregnancy; and the presence of any neurological, cardiovascular, and rheumatological changes or any changes that compromise the understanding of the procedure and affect physical therapy tests and treatment [15, 31].

These individuals will be recruited through posters set up on the campus of the Universidade Federal de Uberlândia (UFU), and by dissemination via social networks and radio in the city of Uberlândia, with the purpose of informing and arousing the participatory interest in the desired population.

This research will be developed in the Laboratório de Avaliação em Biomecânica e Neurociências (LABiN) and the Physical Therapy Clinic School of UFU, Brazil.

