### Intervention/control

Ninety patients will be randomly allocated into two groups: (1) Strengthening Group (SG): submitted to strengthening exercises of the muscle trunk, hip, and knee; and (2) Neuromuscular Training Group (NMTG): submitted to the same protocol as the SG, with the addition of neuromuscular exercises on stable and unstable ground.

Both groups will be submitted to physiotherapeutic treatment for a period of 12 weeks, performing two sessions per week, totaling 24 sessions, with a duration of 60–90 min per session. Each session will consist of 10 min of warming up on elliptical equipment, with a comfortable velocity for the patient and mild-moderate intensity, followed by protocol exercises, as described (see Additional file 1).

Mandatorily, during the first 2 weeks of treatment and/or in the presence of pain, the proposed exercises will be performed within the “protection range” of the patellofemoral joint, with 90–45° of knee flexion during exercises in Open Kinetic Chain (OKC) and 0–45° of knee flexion during Closed Kinetic Chain (CKC) exercises [39]. With the exception of squatting (“wall squat”), it will be performed between 0° and 60° of knee flexion [40]. From the third week, the range of motion of knee flexion will be progressed (in exercises “seated knee extension,” “leg press,” and “wall squat”). This progression will only be performed when the patient has no pain (VAS score 0) or feels only discomfort (VAS score 1) above the protection range of the patellofemoral joint. If the patient experiences pain (VAS score 2 or more) when progressing through the range of motion, the patient will be asked to perform the exercise as much as possible in a pain-free or discomforting (VAS score 0–1) range of motion. If unable to increase the range of motion the exercise will be kept within the protection range of the patellofemoral joint (90–45° for OKC; and 0–45° for CKC) until the pain has resolved.

The initial load during training will be standardized at 70% of 1 repetition maximum (1RM) – defined as the maximum load at which a patient can perform only one repetition of the exercise with good quality and without pain or the need to compensate. One repetition maximum of the exercises will be determined on the first day of care and revised each week for possible adjustments and changes in the load for all exercises. Only the “wall squat” exercise will be started with a load corresponding to 10% of the body weight of each patient.

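### Pre-post tests within each arm at P ≤ 0.05 sit beside the between-group model and can earn effect-size labels, although only the between-group difference addresses the hypothesis

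*Protocol article*

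**What the plan says.** The Background states a comparative hypothesis: "compared to the group that received only strength training", the combined arm "would show greater improvement in pain, function, lower-limb and trunk kinematics" and also in strength.

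The Data analysis section plans two kinds of test for parametric data:

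- Between arms: "comparison between the groups will be carried out using linear mixed models", at P ≤ 0.05.
- Within arms: "For intragroup comparison (pre and post intervention), the analysis of variance (ANOVA) test will be used for repeated measurements", also at P ≤ 0.05.

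The within-arm tests are not called descriptive or supportive. The next paragraph calculates Cohen's d for whichever differences prove significant and grades it small, medium or large as confirmation of clinical relevance. It does not limit this to between-arm differences.

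Under Study design there are two assessments, before and after the 12 weeks. Under Participants and therapists, women enter "with a Visual Analog Scale (VAS) score ≥ 3".

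**The concern.** Both arms receive the same 12-week strengthening programme, and the Discussion describes strengthening as an established treatment that already works. Change from baseline is therefore expected in each arm whatever neuromuscular training adds. For pain, selecting women above a VAS threshold adds regression to the mean.

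A within-arm P value asks whether an arm changed. The hypothesis asks whether one arm changed more than the other. If the training arm reaches P ≤ 0.05 and the strengthening arm does not, the pair of results looks like added benefit, yet it can arise by chance between equal treatments. The Cohen's d sentence adds to this: as worded, one arm's change could be graded as clinically relevant while the other's gets no grade. The stake is the trial's single question.

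**Working it through.** **The plan's own figure.** The article states: "The power of the test considered was 80% and the alpha was 0.05, with a sample size of 45 per group". It gives no numerical mean difference or SD, so 45 cannot be reproduced. Solved backwards (two-sided, normal approximation), d = √(2/45) × (1.960 + 0.842) = 0.2108 × 2.802 = 0.59. The t-based value is 0.60 and the one-sided value 0.52. The point below does not depend on this.

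**Inputs.**

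- n = 45 per arm and alpha 0.05, from Participants and therapists. Sidedness is not stated there; two-sided is assumed.
- Two time points, from Study design. A repeated-measures ANOVA within one arm is then equivalent to a paired t-test (F = t²).
- Equal true change in both arms: the scenario under test.
- Standardised change dz = mean change / SD of change. The article gives no value, so a range from 0 to 1.0 is shown. If the pre-post correlation is 0.5, SD of change = SD × √(2(1 − 0.5)) = SD, and dz is then also the change in baseline SDs.

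**Formulas.** Within-arm power p comes from the noncentral t distribution with 44 degrees of freedom and noncentrality dz × √45. The arms are independent, so P(exactly one arm significant) = 2p(1 − p).

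| dz | p | 2p(1 − p) |
|---|---|---|
| 0 | 0.050 | 9.5% |
| 0.1 | 0.101 | 18% |
| 0.2 | 0.259 | 38% |
| 0.3 | 0.503 | 50% |
| 0.4 | 0.747 | 38% |
| 0.5 | 0.907 | 17% |
| 0.6 | 0.976 | 5% |
| 0.8 | 0.999 | 0.1% (from unrounded p) |
| 1.0 | 1.000 | about 0% |

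Worked line, dz = 0.3: 2 × 0.503 × 0.497 = 0.500. In half of these cases (25% of trials) the significant arm is the training arm.

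**Simulation check.** With 40,000 trials per setting, disagreement was 39.0, 50.3, 37.7, 17.0, 0.1 and 0.0% at dz = 0.2, 0.3, 0.4, 0.5, 0.8 and 1.0. A two-sample t-test comparing change between arms in the same data was significant in 4.7 to 5.1% of trials, which is its nominal rate.

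**Sensitivity to fewer women.** If 20% lacked a second assessment (an assumption), 45 × 0.8 = 36 per arm would remain. Disagreement would then be 49% at dz = 0.3, 28% at 0.5, 12% at 0.6 and 0.7% at 0.8. The pattern is the same, shifted slightly towards larger changes.

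**The case against.** The strongest reply is that the right comparison is already there. The between-group model comes first, the hypothesis is comparative, and nothing in the article says that within-arm P values will decide whether neuromuscular training helps. Describing change under each programme is a legitimate aim. All of this stands, and it limits the point to a risk of misreading. It does not remove the point, because the article gives these tests their own significance threshold and lets their results qualify for a clinical-relevance grade.

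The second reply is that disagreement between arms depends on the assumed change. This also stands. The article expects strengthening to work, so pain and function may well change by more than 0.6 standardised units, where disagreement is rare.

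A reader might go further in three ways that the article does not support:

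- **Conflict with intention-to-treat.** Repeated-measures ANOVA needs both measurements, so one might infer that women without a post-test are dropped. The article states intention-to-treat but does not show how missing values are handled. With imputation nobody need be dropped, and a condensed article may leave that detail to the full plan.
- **A multiplied error rate.** One might count the within-arm tests as tripling the P values. The article does not say which model terms are tested, and satisfaction is asked only at reassessment, so the count is unknown. The within-arm tests also leave the between-group error rate unchanged, as the simulation shows.
- **Regression to the mean everywhere.** Entry is selected on pain. That supports the argument for the VAS, but not clearly for kinematics or strength.

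**Conclusion.** The point holds as a matter of wording and interpretation that should be corrected. The planned within-arm tests cannot show what neuromuscular training adds, whatever their result.

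Under equal treatments, 45 per arm and two-sided tests, the chance that exactly one arm is significant lies between 17% and 50% per outcome for standardised changes of 0.1 to 0.5. It is about 5% at 0.6 and negligible from 0.8. The size of change is assumed throughout. The misleading pattern is therefore a practical threat for outcomes that change little, perhaps some kinematic angles. For outcomes that improve strongly, both arms will be significant and the tests say nothing about the comparison.

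It would be too strong to conclude that the trial lacks a valid primary comparison or intends to rely on within-arm results. Neither is in the text.

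**What to change.** In Data analysis, replace the intragroup tests with a statement that within-arm mean change will be reported with a 95% confidence interval, as description and without P values. State that every claim about neuromuscular training rests on the between-group difference in change from the planned mixed model, and name the term that carries it: the group-by-time effect or the baseline-adjusted difference. Limit the Cohen's d sentence to that between-group difference. If an outcome takes the non-parametric route, apply the same restriction there.

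The cost is a change of wording and fewer P values in a table. Recruitment, assessments and sample size are untouched.

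### Cohen's d is calculated only for significant differences, which biases it upward on average, and its bands set no threshold for clinical relevance

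*Protocol article*

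**What the plan says.** The protocol article, under Data analysis, plans that "comparison between the groups will be carried out using linear mixed models" and that pre-post changes within each group will be tested by repeated-measures ANOVA. Both use "values ≤ 0.05 as significant difference". The next paragraph sets the rule for relevance: "The clinical relevance of the results will be confirmed by calculating the effect size (Cohen’s d) of the significant differences". It grades d as "0.00–0.49, small; 0.50–0.79, medium; and above 0.80, large".

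The article gives no other criterion for clinical relevance. It names no minimal important difference for the VAS, AKPS or ADLS, and no value of d below which a result counts as not relevant. The rule follows both kinds of comparison and excludes neither.

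On size, Participants and therapists states: "The power of the test considered was 80% and the alpha was 0.05, with a sample size of 45 per group". The mean difference and SD behind that number are attributed to similar studies and are not given.

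**The concern.** This is a stated rule, not a detail left to a fuller document, and it has three weaknesses.

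- **Selection.** The effect size is calculated only when the P value passes 0.05. At a given sample size, passing depends on the estimate being large, so the reported values of d come from the upper part of their distribution.
- **No threshold.** The step is meant to confirm relevance, but the lowest band starts at 0.00 and no band means negligible or not relevant. Whatever d turns out to be, the rule cannot return the answer that a significant result is not clinically relevant.
- **Yardstick.** In an unadjusted comparison at fixed n, d is the t statistic multiplied by a constant, so it adds little to the P value. It is in SD units and is not linked to a change on the VAS, AKPS or ADLS that a patient would find worthwhile.

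Both arms receive the same strengthening programme, and the Background reports that the one earlier study of the added component found no significant kinematic benefit. Small true effects are therefore plausible, and the selection bias is largest for small effects. The Discussion intends the results to inform treatment decisions, so the size and relevance of the effect matter as much as its P value.

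**Working it through.** **Inputs from the article:** 45 per group, alpha 0.05, power 80% (Participants and therapists); P ≤ 0.05 as the filter, and the bands for d (Data analysis).

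**Assumptions:** two-sided test (the article does not say), equal arms, no dropout, normal data.

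**1. The plan's own figure.** The 45 per group cannot be reproduced, because no mean difference or SD is stated. Solving backwards for the effect it implies:

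d = (z₀.₉₇₅ + z₀.₈₀) × √(2/n) = (1.960 + 0.842) × √(2/45) = 2.802 × 0.2108 = 0.59.

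The noncentral t gives 0.60. A one-sided test would give 0.52 (0.53 by noncentral t). A true d of about 0.6 is therefore the reference case for the two-sided design.

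**2. Smallest between-group d that can be reported.**

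d_min = t(0.975; 88) × √(2/45) = 1.987 × 0.2108 = 0.419.

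With baseline adjustment this is multiplied by √(1 − r²), where r is the pre-post correlation. The article gives no r. At an assumed r of 0.3, 0.5 and 0.7 the floor is 0.40, 0.36 and 0.30.

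**3. Smallest pre-post d that can be reported**, on the raw-SD scale:

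d_min = t(0.975; 44)/√45 × √(2(1 − r)) = 0.300 × √(2(1 − r)).

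This is 0.36 at an assumed r of 0.3 and 0.13 at 0.9.

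**4. Mean reported d given significance.** 400,000 trials were simulated per true d, with 45 per arm and an unadjusted two-sided test at 0.05.

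| True d | Power | Mean d, all trials | Mean d, significant only | Ratio to truth | Significant estimates below truth | Significant results graded small |
|---|---|---|---|---|---|---|
| 0.2 | 16% | 0.20 | 0.52 | 2.6 | 1% | 47% |
| 0.3 | 29% | 0.30 | 0.555 | 1.85 | 0.1% | 39% |
| 0.5 | 65% | 0.505 | 0.63 | 1.25 | 23% | 23% |
| 0.6 | 80% | 0.605 | 0.68 | 1.13 | 37% | 15% |
| 0.8 | 96% | 0.81 | 0.825 | 1.03 | 48% | 4.5% |

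With no true effect, the 5% of results that are significant have a mean |d| of 0.50. About 60% of them are graded small and 40% medium or large.

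The third column is the control. When d is calculated for every comparison, its mean is almost equal to the truth, so nearly all of the excess in the fourth column comes from the filter.

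**5. Can the rule return a negative answer?** The bands start at 0.00 and run upward without a level meaning not relevant. No significant result can be rejected as irrelevant under the rule as written.

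**The case against.** Several points on the other side are sound.

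- **A reader might infer that every reported effect is inflated.** It is not. The bias is an average: at a true d of 0.6, 37% of significant estimates lie below the truth, and at 0.8, 48% do. The 2.6-fold figure belongs to a true d of 0.2, where power is only about 16%. At the effect the design implies, the inflation is about 13%.
- **A reader might infer that every significant result is declared clinically relevant.** The article grades significant results and never says that small means relevant. What the text supports is narrower: no threshold is fixed, so nothing can be judged not relevant.
- **A reader might infer that null results are hidden, or that the trial cannot answer its practical question.** The rule restricts only Cohen's d. It does not say that mean differences or intervals will be withheld, a mixed model estimates a difference for each outcome it is applied to, and reporting format is commonly left to a fuller document.
- **The calculation is not the planned analysis.** It uses an unadjusted t test where the article plans mixed models. This stands, and the lower floors under step 2 show how much it could matter.
- **The band starting at 0.00 rarely bites between groups**, since no unadjusted |d| below 0.42 is significant. This also stands, but it does not supply the missing threshold. Pre-post floors can be much lower.

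It also cannot be checked here whether the instrument papers that the article cites contain minimal important differences.

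**Conclusion.** The concern holds in limited form. Calculating d only for significant differences biases the reported d upward on average: by about 13% near the design-implied effect of 0.6, about 3% at 0.8, and much more if the true effect is small (mean 0.52 for a true 0.2). These figures assume an unadjusted two-sided comparison with 45 per group and no dropout. Baseline adjustment would lower the 0.42 floor.

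Separately, and without depending on any simulation, the rule offers as confirmation of clinical relevance a scale that has no level for not relevant and no link to a worthwhile change on the VAS, AKPS or ADLS. The P-value tests themselves are unaffected. The wording should be changed, but the fault does not invalidate the trial.

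**What to change.** Remove the sentence that makes Cohen's d the confirmation of clinical relevance, and replace it with the following.

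1. For every primary and secondary scale or measurement outcome, significant or not, report the between-group mean difference from the mixed model in scale units with its 95% CI.
2. If d is kept, report it for all of these outcomes as a descriptive figure only.
3. Judge the clinical relevance of the VAS, AKPS and ADLS results by comparing that CI with a minimal important difference for each scale. The investigators fix and justify these values before analysis.

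The change affects analysis and reporting wording only and needs no further participants or measurements. The investigators must do the work of choosing and defending the minimal important differences. The downside is that some significant results will be reported as not clinically relevant.
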